### 2.1. Study Design

This randomized controlled trial (RCT) with a qualitative component is designed to assess the effectiveness of the TSR intervention for individuals affected by leprosy in Addis Ababa, Ethiopia.

Methodological features of this feasibility RCT will minimize the possible bias in the intervention group. These features include allocation concealment (that will be ensured by randomization to be performed by an independent, off-site statistician), blinding (study statistician and the research team carrying out follow-up assessments will be masked to treatment allocation), use of intention-to-treat analysis, and the use of primary versus secondary endpoints.

The study will involve two arms: an intervention group receiving the TSR intervention and a waitlist control group. Participants will undergo individual randomization conducted by an off-site statistician. A total of 100 participants will be randomized in a 1:1 ratio into either the TSR intervention group (*n* = 50) or the waitlist control group (*n* = 50). Randomization will occur after baseline assessments using a computer-generated sequence to ensure allocation concealment.

As this study first of its kind and aims to demonstrate a trend in favor of the intervention and the recruitment and retention of participants into the study, the sample size was informed by community consultation and trial guidelines [20–25] to ensure a sample that allows for the estimation of recruitment and retention parameters, as well as potential effectiveness.

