Participants will be included in the study if they meet the following criteria: (a) aged over 18 years, (b) able to give written informed consent—individuals with physical disabilities that may limit their ability to provide written consent will be permitted to give verbal consent, (c) leprosy-affected persons residing in the research sites, (d) score positive for depression on the Patient Health Questionnaire (PHQ-9), and (e) registered with a local health service. Although, to the best of our knowledge, there is no systematic mental health support specifically designed for individuals affected by leprosy, the limited available care may include counseling, therapeutic interventions, and pharmacological treatment, based on the severity of the condition. Such services are predominantly accessible within hospitals. However, these resources are frequently inadequate in rural regions, where both clinical expertise and diagnostic capabilities are often lacking. Consequently, individuals currently receiving any form of mental health support, such as individual or group psychotherapy, will be excluded from the study, as such interventions may confound the outcomes. Furthermore, individuals presenting with dissociation, psychosis, suicidal ideation, or substance use disorders will be deemed ineligible for participation. All participants will receive compensation for their time and contribution on a per-session basis.

Participants will be recruited from community settings where persons affected by leprosy reside, in partnership with organizations of persons affected by leprosy, with whom The Leprosy Mission Ethiopia have a long-standing working relationship such as ALERT Hospital and Ethiopian National Association of Persons Affected by Leprosy (ENAPAL).

Participants will also be recruited via referrals, and announcements will be shared with relevant organizations. Stakeholder engagement exercises will be conducted. Snowball sampling will be employed to initiate contact and encourage trial participation.

Eligible participants expressing interest in further information will be contacted by a member of the research team and provided with information about the study. This will include the aims of the study and a participant information sheet.

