### 2.3. Data Collection

#### 2.3.1. Outcomes

The primary outcomes will be the changes in PTSD, anxiety, and depression symptoms, and levels of social support from baseline to postintervention. Secondary outcomes will include participant satisfaction and insights derived from the qualitative data.

Participants will complete a battery of self-report questionnaires at three time points: baseline (T0), postintervention (T1), and at a 1-month follow-up. The assessment includes the International Trauma Questionnaire (ITQ), Generalized Anxiety Disorder 7-item scale (GAD-7), PHQ-9, Health Questionnaire (EQ-5D-5L), the Oslo Social Support Scale (OSSS-3), and 5-Question Stigma Indicator—Affected People.

In addition to the quantitative assessments, a qualitative component will be included postintervention. Semistructured interviews will be conducted with participants from both the intervention and control groups to explore their experiences and views regarding the TSR intervention and standard care, respectively. This qualitative data will provide deeper insights into the feasibility, acceptability, and effectiveness of the intervention.

The sociodemographic questionnaire will collect essential background information about the participants, including age, gender, marital status, education level, employment status, and duration of leprosy diagnosis. These data are crucial for understanding the context in which participants live and how various demographic factors might influence their mental health outcomes. The sociodemographic information will help in identifying potential correlations between participants' backgrounds and their responses to the intervention, ensuring that any observed effects are appropriately contextualized.

The quantitative data will be analyzed using intention-to-treat principles, with comparisons between the intervention and control groups, whereas the qualitative data will be analyzed using the reflexive thematic analysis [32–35].

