### 2.4. Data and Management

Summary statistics, means, medians, counts, and percentages along with corresponding measures of variability will be reported, along with 95% confidence intervals. The information gathered on the variability of the outcome measures will be sufficient to allow a formal sample size calculation to be made for the subsequent definitive RCT. The proportion of participants recruited and retained in the study will be reported along with 95% confidence intervals. A sample size of 100 will allow the recruitment/retention rates to be estimated with an accuracy of ± 8%.

One-way repeated measures analysis of variance to elucidate the impact of interventions on scores on all outcome tools while accounting for baseline characteristics of participants such as age, gender, and baseline severity of psychological symptoms will be employed. Mean and SD and effect sizes calculated as Cohen's d noted in this trial will inform sample size calculation for future definitive trials. The project will also have a clear Stop-Go criterion:• If the retention rate is 70% or higher, we will proceed with the full RCT as it is feasible.• If the retention rate is between 50% and 70%, we will explore methods to increase the retention rate to the required 70%. Alternatively, we may increase the required sample size to account for the higher drop-out rate.• However, if the recruitment rate is less than 50%, a full trial may not be feasible. In such cases, alternative approaches will be considered.

Subgroup analysis will be carried out with respect to age, duration of illness, number of previous episodes, and gender by adding a treatment with covariate interaction into the primary analysis model.

Data will be initially stored in a secured office location and subsequently digitized for storage on a secure network. In addition, all project-generated data will be assigned unique codes to protect participant confidentiality. Data associated with these codes and any identifiable information will be stored separately.

Descriptive statistics will be conducted for baseline and postintervention measures, including mean scores, standard deviations, and ranges. In addition, recruitment, attendance, and dropout rates will be reported to assess feasibility and acceptability.

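### The only outcome model named, a one-way repeated measures ANOVA, has no arm term and conflicts with the between-arm comparison that the protocol promises elsewhere

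*Protocol article*

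**What the plan says.** The design in section 2.1 of the protocol article is a parallel-group trial: "The study will involve two arms: an intervention group receiving the TSR intervention and a waitlist control group". Fifty people are randomised to each arm.

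Section 2.3.1 defines the primary outcomes as changes between baseline and the postintervention assessment, and states: "The quantitative data will be analyzed using intention-to-treat principles, with comparisons between the intervention and control groups".

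Section 2.4 then names the model: "One-way repeated measures analysis of variance to elucidate the impact of interventions on scores on all outcome tools". The sentence continues "while accounting for baseline characteristics of participants such as age, gender, and baseline severity of psychological symptoms will be employed". Age, gender and baseline severity are listed; arm is not. No other model for the outcome scores appears in the article. The ANOVA is not itself labelled primary; that follows only because it stands alone.

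Two further sentences of section 2.4 depend on this model or its results. Subgroup effects are to be examined by "adding a treatment with covariate interaction into the primary analysis model". Means, SDs and Cohen's d from this trial are to feed the sample size of the definitive trial.

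**The concern.** In ordinary usage, one-way repeated measures means one within-person factor, here time. Its F-test asks whether mean scores differ between visits. It does not ask whether they moved further under TSR than under waitlist, which is the question the randomisation was set up to answer.

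If an analyst follows the label, improvement that would have happened anyway counts as a result of the programme. Two sources are plausible. One is natural recovery over the study period. The other is regression to the mean on the PHQ-9: entry requires a positive score, so the mean would be expected to fall if the screening score also serves as the baseline score.

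A stated purpose of the trial is to plan a larger one. A Cohen's d taken from pre-post change would carry the shared improvement into that calculation and make the next trial too small.

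**Working it through.** **1. The statements side by side**

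| Place | What it requires |
|---|---|
| Section 2.1, two randomised arms | a contrast between arms |
| Section 2.3.1, analysis sentence | a contrast between arms, by intention to treat |
| Section 2.4, named model | one factor, time; no arm, no arm-by-time |
| Section 2.4, subgroup sentence | a treatment term already in the primary model |

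The third row cannot be reconciled with the other three. No sentence says which term gives the treatment estimate.

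**2. What each test estimates**

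Let both arms fall by *m* for reasons unrelated to TSR, and let TSR add a further fall δ.

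- Mean change in the TSR arm: −(m + δ)
- Mean change in the waitlist arm: −m
- Time effect, arms pooled 1:1: −(m + δ/2)
- Time effect, TSR arm only: −(m + δ)
- Arm-by-time effect: −(m + δ) + m = −δ

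With δ = 0 the time effect is −m, and the between-arm effect is 0 whatever *m* is.

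**3. Size**

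The protocol gives no figure to reproduce here: no alpha, SD, pre-post correlation or expected waitlist change. From the protocol: 50 per arm, two visits. Assumed: two-sided 5%, scores in SD units, correlation ρ of 0.5 or 0.7, shared fall *m* of 0 to 0.5 SD, δ = 0. Results are from 4,000 simulated trials per setting.

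| ρ | m (SD) | Time test, pooled | Time test, TSR arm | Arm-by-time | ANCOVA |
|---|---|---|---|---|---|
| 0.5 | 0 | 5.4% | 5.1% | 4.8% | 4.8% |
| 0.5 | 0.2 | 51.5% | 28.2% | 4.7% | 4.6% |
| 0.5 | 0.3 | 84.0% | 54.8% | 4.9% | 4.9% |
| 0.5 | 0.5 | 99.8% | 93.6% | 5.1% | 5.4% |
| 0.7 | 0 | 5.4% | 4.5% | 4.9% | 4.9% |
| 0.7 | 0.2 | 72.3% | 42.8% | 5.2% | 4.8% |
| 0.7 | 0.3 | 97.1% | 76.0% | 5.0% | 4.6% |
| 0.7 | 0.5 | 100% | 99.5% | 4.5% | 4.5% |

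Hand check of one cell: with two visits, F = t², where t = mean change ÷ (SD of change/√n) and SD of change = √(2(1 − ρ)). At ρ = 0.5 this SD is 1. With n = 100 and m = 0.2, the expected t is 0.2 × 10 = 2.0, and Φ(2.0 − 1.96) ≈ 52%, in line with 51.5%.

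**4. Effect on Cohen's d**

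With m = 0.3, ρ = 0.5 and a true between-arm effect of 0.5 SD, the average standardised change within the TSR arm is 0.80, while the adjusted between-arm difference averages 0.50. Required sample size is proportional to 1/d², so planning on 0.80 would give (0.50/0.80)² = 0.39 of the number needed for 0.50.

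**5. Is a shared fall to be expected?**

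Table 1 lists the eligibility screen before the t0 assessment and schedules the PHQ-9 at t0. It does not say whether the screening PHQ-9 is reused as baseline. For illustration, assume a cut-off of 10, population mean 8, SD 5 and reliability 0.7. Those selected average 5.34 points above the population mean.

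- Screening score reused as baseline: expected fall (1 − 0.7) × 5.34 = 1.6 points; the time test rejects in about 99% of null trials (pooled) and 85% (TSR arm).
- Baseline measured separately: fall about 0; the time test rejects in about 5%.

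Selection is on the PHQ-9 only, so regression to the mean on the other scales would be indirect and smaller.

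**The case against.** The strongest reply is that the between-arm intention is plain. Section 2.3.1 promises the comparison, and the subgroup sentence makes sense only if treatment is already in the model. The adjusters in section 2.4 are between-person variables, so the model is not literally a one-way within-person ANOVA. The trial is exploratory, its Stop-Go rule uses retention and recruitment rather than this test, and the text does not tie Cohen's d to the ANOVA.

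All of that stands, and it makes the bias conditional on following the label. It does not repair the sentence: to say that a two-way or mixed design was meant is to concede that the named model is wrong.

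Some stronger readings are tempting and should not be drawn:

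- *The plan contains no between-arm comparison.* Section 2.3.1 and the subgroup sentence say otherwise; this is a misnamed model and an internal contradiction.
- *An ineffective programme would usually look effective.* That needs both the literal model and a shared fall, and the documents establish neither.
- *Baseline is wrongly used twice.* With two visits and an arm term, regressing (post − baseline) on arm and baseline gives the same arm coefficient as regressing post on arm and baseline; only the baseline slope shifts by 1. The overlap is harmless for the arm estimate.
- *Repeated measures ANOVA breaks intention to treat by dropping incomplete cases.* With only baseline and postintervention scores, ANCOVA needs the same two values from the same people. A difference arises only if the 1-month visit, mentioned in section 2.3.1 but absent from Table 1, is kept.
- *ANCOVA brings a large gain in power.* For a 0.5 SD effect, simulated power of ANCOVA against the arm-by-time test is 81.5% against 69.8% at ρ = 0.5 and 92.8% against 88.3% at ρ = 0.7. In the selection example of working step 5, with the screen as baseline and a 2.5-point effect, it is about 93% against 92%. The protocol gives no basis for choosing among these.

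**Conclusion.** The concern holds as an error of specification. The one model named for the outcomes cannot deliver the comparison that the same article commits to, and section 2.4 is inconsistent with itself. That conclusion needs no assumed numbers.

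The consequence is conditional. If the label is followed and scores fall in both arms, the false-positive rate of the time test lies far above 5%, over the ranges tabulated above, and a within-arm d is too large by the shared fall. If there is no shared fall, the literal test holds its level with no TSR effect, but it still does not estimate the randomised contrast. The rejection rates depend on the assumed fall and correlation; the direction does not.

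**What to change.** Replace the model sentence in section 2.4 with wording along these lines:

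*Each outcome score at the postintervention assessment will be compared between the arms as randomised, using analysis of covariance with arm, the baseline value of that outcome, age and gender. The estimate is the adjusted between-arm difference with its 95% confidence interval. Cohen's d for planning the definitive trial will be based on this difference, and subgroup interactions will be added to this model.*

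If the 1-month visit is kept, use the equivalent mixed model for the post-baseline scores, with arm, visit and arm-by-visit, and the baseline value as a covariate. State also whether the screening PHQ-9 serves as the baseline PHQ-9.

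The cost is wording only: no additional participants, visits or data.

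### The only outcome model named, a one-way repeated measures ANOVA, has no TSR-versus-waitlist term as written, so it contradicts the between-arm comparison and the subgroup model that the protocol promises

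*Protocol article*

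**What the plan says.** Section 2.4 (Data and Management) names one inferential analysis for the outcomes: "One-way repeated measures analysis of variance to elucidate the impact of interventions on scores on all outcome tools". It is to be run "while accounting for baseline characteristics of participants such as age, gender, and baseline severity of psychological symptoms will be employed". Arm is not in that list, and neither an arm-by-time term nor a between-arm contrast is named.

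Other parts of the article assume an arm comparison:
- Section 2.1 describes two arms randomised 1:1, 50 to TSR and 50 to waitlist.
- Section 2.3.1: "The quantitative data will be analyzed using intention-to-treat principles, with comparisons between the intervention and control groups". No model is attached to this sentence.
- Section 2.4, on subgroups: these are to be examined "by adding a treatment with covariate interaction into the primary analysis model".

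Section 2.4 also says that Cohen's d from this trial will feed the sample size of the definitive trial. It does not say whether d is between arms or before versus after. Entry requires a positive PHQ-9 (2.1), and change in depression is among the primary outcomes (2.3.1).

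**The concern.** The label one-way repeated measures describes a design with one factor, measured within persons, which here is time. Such a model asks whether mean scores differ between visits. It does not ask whether TSR participants change more than waitlist participants, and that is the question the trial randomises to answer.

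Two things are at stake. First, scores can fall in both arms without any treatment effect, through natural recovery or through regression to the mean after selection on a high PHQ-9. A time-only test cannot separate that fall from an effect of TSR. Second, a d computed from change over time mixes the common fall with the treatment effect. If that figure is carried forward, the definitive trial could be planned on too large an effect.

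**Working it through.** **Consistency of the text.** What each statement needs from the model:

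| Statement | Needs | Supplied by a one-way repeated measures ANOVA? |
|---|---|---|
| Comparison of arms (2.3.1) | Arm term, or arm-by-time term | No |
| Treatment-by-covariate interaction in the primary model (2.4) | Treatment main effect to build on | No |
| Adjustment for age, gender, baseline severity (2.4) | Covariates | They can be added, but they do not bring in arm |

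The protocol states no power or effect figure for the outcome analysis, so there is none to reproduce.

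**Size of the problem if the model is applied literally (PHQ-9).** From the article: 100 participants, 50 per arm. The introduction gives 14% (moderate to severe depression) and 34.6% (mental health difficulties) as prevalence figures in persons affected by leprosy; these stand in for the share screening positive. Assumed: 50% as an upper share, normal scores in SD units, T0–T1 correlation ρ of 0.6 to 0.8, the screening score reused as T0, two visits, two-sided 0.05, no TSR effect.

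With share p above cut-off c:
- mean of T0: λ = φ(c)/p
- variance of T0: v = 1 + cλ − λ²
- mean fall from T0 to T1 in either arm: (1 − ρ)λ
- SD of the change: √[(1 − ρ)²v + 1 − ρ²]
- expected t, approximately: √n × fall / SD

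| p | ρ | λ | v | Fall | SD of change | t, n=100 | t, n=50 | Rejects, pooled | Rejects, TSR arm |
|---|---|---|---|---|---|---|---|---|---|
| 0.50 | 0.8 | 0.798 | 0.363 | 0.2×0.798 = 0.160 | √(0.04×0.363+0.36) = 0.612 | 2.61 | 1.84 | 73% | 44% |
| 0.346 | 0.7 | 1.066 | 0.286 | 0.3×1.066 = 0.320 | √(0.09×0.286+0.51) = 0.732 | 4.37 | 3.09 | 99% | 86% |
| 0.14 | 0.6 | 1.590 | 0.190 | 0.4×1.590 = 0.636 | √(0.16×0.190+0.64) = 0.819 | 7.77 | 5.49 | about 100% | about 100% |

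Simulation of 4,000 trials per setting gives the same ranges. In the same data an ANCOVA with arm and baseline rejects in about 5%.

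**Natural recovery alone.** With no selection, ρ = 0.7 and a 0.3 SD fall in everyone, the SD of change is √(2×0.3) = 0.775. The expected t is 0.3/0.775 × 10 = 3.87 pooled and 0.3/0.775 × √50 = 2.74 in the TSR arm. Simulated rejection is 97% and 76%, against about 5% with an arm term.

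**Sensitivity to how T0 is obtained.** Table 1 lists the eligibility screen at −t1 and the baseline PHQ-9 at t0, and does not say whether one score serves for both.
- If PHQ-9 is re-measured at T0 and all three occasions are equally correlated, the means at T0 and T1 are both ρλ. The fall is zero and the time-only test rejects in about 5%.
- If it is re-measured but the screening score correlates 0.9 with T0 and is linked to T1 only through T0, the fall is 0.9(1 − ρ)λ. Rejection is again high, 64% to 100% pooled and 34% to 100% in the TSR arm.

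**Scales not used for entry.** For an outcome correlated 0.3 to 0.5 with PHQ-9 (ρ of 0.6 or 0.8), the time-only test in the TSR arm rejects in about 9% to 71%.

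**Cohen's d.** At p = 0.346 and ρ = 0.7, a true TSR effect of 0.50 SD gives a fall in the TSR arm of 0.32 + 0.50 = 0.82 SD, while the between-arm difference is 0.50 SD. Required sample size varies as 1/d². With the same SD in the denominator, planning on 0.82 gives (0.50/0.82)² = 0.37 of the participants needed for 0.50.

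**The case against.** The strongest reply is that an arm comparison is plainly intended. Section 2.3.1 says so, the subgroup sentence presupposes a treatment term, the trial is randomised with a masked statistician, and 2.4 never says that time is the sole factor. The term may be a mislabel for a model that does contain arm, and a statistical analysis plan that is not shown may set this right. The go/no-go rule uses retention and recruitment rather than this test, and the trial is exploratory.

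Much of this stands. A reader might infer that the trial will report a false benefit of TSR. The documents do not support that: it follows only if the named model is used literally and alone. A reader might also take a fall in both arms as certain. Regression to the mean depends on whether the screening score doubles as T0, which Table 1 leaves open, and it is weaker for ITQ, GAD-7 and EQ-5D-5L, which are not entry criteria.

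One could further object that a repeated measures model with T0 both as a level and as a covariate halves the arm main effect. The protocol names no such model, and the arm-by-time term in it would recover the full effect, so that is not part of this point.

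What the reply does not remove is the contradiction. The article did not leave the model to a later document. It named one, and that model does not fit its own statements elsewhere.

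**Conclusion.** Wrong as written. This is a misstated method rather than missing detail: the only inferential outcome model in 2.4 has no arm term, and it conflicts with 2.3.1 and with the subgroup sentence in 2.4 itself. That conclusion rests on the text alone.

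The consequence is conditional. If the sentence is followed literally, a change common to both arms could be read as the impact of TSR. The 73% to 100% (pooled) and 44% to 100% (TSR arm) rates apply to PHQ-9 under the stated assumptions, above all reuse of the screening score as T0, and can drop to about 5% without it. They illustrate a risk and do not predict the result. The unspecified Cohen's d matters most for what follows, because it is meant to inform the definitive trial's sample size.

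**What to change.** In 2.4:
1. Replace the one-way repeated measures ANOVA with a model for the postintervention (T1) score, with arm as the factor of interest and that outcome's own baseline score, age and gender as covariates. ANCOVA does this; so does a mixed model whose primary contrast is the arm difference at T1.
2. State that Cohen's d is computed from the adjusted between-arm difference at T1.
3. State that the subgroup interactions are added to this model.

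For outcomes measured at both T0 and T1 this costs only wording, with no extra data or participants. It cannot yet be applied to social support. Section 2.3.1 makes change in social support a primary outcome and lists OSSS-3 in the battery for three time points, but 2.3.1.5 and Table 1 give it at baseline only. Those places must be reconciled first, and collecting OSSS-3 at T1 would be a change to the schedule.

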The current project will test TSR's potential effectiveness in reducing symptoms of PTSD, anxiety, and depression. Specifically, it will evaluate the feasibility of recruiting individuals with leprosy for the TSR intervention, assessing its acceptability through various parameters such as recruitment rates, participant engagement, session attendance, and dropout rates. Qualitative interviews will further explore these aspects. The study will also define appropriate primary and secondary outcomes for assessing the intervention's effect in a full-scale trial. Data from this study will inform the design of a future multisite definitive clinical trial, including optimizing the design and planning the sample size. By focusing on this underserved population, the study aims to fill a critical gap in the literature and provide a foundation for future research on the effectiveness of mental health interventions for individuals with leprosy. The findings will have significant implications for public health strategies in similar contexts and could lead to the development of more comprehensive care models that address both the physical and psychological needs of individuals affected by leprosy.

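### The observed Cohen's d is listed as an input to the definitive sample size with no target difference named, and at 35 to 50 per arm it is too imprecise for that use

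*Protocol article*

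**What the plan says.** Section 2.4 (Data and Management) states: "Mean and SD and effect sizes calculated as" Cohen's d "noted in this trial will inform sample size calculation for future definitive trials". The Introduction makes this kind of planning a purpose of the study, "including optimizing the design and planning the sample size", without mentioning d. Section 2.3.1.8 also counts the ability to calculate a sample size from the feasibility data among the things to be evaluated.

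Earlier in section 2.4 a different basis is given: "The information gathered on the variability of the outcome measures will be sufficient to allow a formal sample size calculation" for the later trial.

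Section 2.1 fixes the size of the present trial: "A total of 100 participants will be randomized in a 1:1 ratio", which is 50 per arm. That number was not derived from a target effect; "the sample size was informed by community consultation and trial guidelines". The only precision attached to it, in section 2.4, concerns proportions: "A sample size of 100 will allow the recruitment/retention rates to be estimated with an accuracy of ± 8" per cent. The article gives no minimum important difference, no external target effect and no allowance for the uncertainty of d.

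**The concern.** A sample size calculation needs a target difference and a set of nuisance parameters (SD, correlation with baseline, attrition). A pilot of this size estimates the nuisance parameters tolerably well and the effect poorly. The Cohen's d sentence adds the poorly estimated quantity to the well estimated one. Since d is the only effect the article mentions for planning, it is the natural candidate for the target difference. The required n depends on the inverse square of d, so a modest error in d becomes a large error in n. An observed d that is too high gives an underpowered definitive trial. One that is too low gives a needlessly large trial, or one abandoned as unaffordable. Sizing the definitive trial is a stated purpose of this study, so a main deliverable is at stake.

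**Working it through.** **The plan's own figure.** The ±8% is a 95% half-width for a proportion, 1.96·√(p(1−p)/100). The article gives no p. At p = 0.80 it is 7.8 points, at 0.79 it is 8.0, and at the 70% retention threshold it is 9.0. The figure reproduces for a rate near 80%, but it says nothing about the precision of d.

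**Inputs.** From the article: 50 per arm (section 2.1), and 70% retention as the threshold to proceed (section 2.4), hence 0.7 × 50 = 35 per arm. Assumed: true d of 0.3, 0.4 or 0.5; two-sided α of 0.05; 80% power; an unadjusted two-arm comparison; a definitive trial sized only when the observed d is positive.

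**Precision of d.** SE(d) = √(2/n + d²/(4n)), with n per arm. At d = 0.4:
- n = 50: SE 0.202, 95% interval 0.00 to 0.80.
- n = 35: SE 0.241, 95% interval −0.07 to 0.87.

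**From d to planned n.** n per arm = 2(1.96 + 0.842)²/d² = 15.7/d².
- d = 0.4: 98.1, so 99, or about 100 with the t correction.
- Observed d one SE high (35 per arm), 0.64: 15.7/0.41 = 38.3, about 40 per arm with the t correction. True power at d = 0.4 is then 42%.
- Observed d one SE low, 0.16: 15.7/0.0256 = 613 per arm, about six times the correct size.

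**How often the planned trial has power below 50%.** This happens when the observed d exceeds the true d by the factor 2.802/1.96 = 1.43. The chance is P(Z > 0.43·d/SE), divided by the chance that the observed d is positive.

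| True d | 50 per arm | 35 per arm |
|---|---|---|
| 0.3 | 28% | 33% |
| 0.4 | 20% | 25% |
| 0.5 | 14% to 15% | 19% |

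Simulated pilots, with the observed d drawn from the noncentral t distribution, agree. At d = 0.4 they give 20% to 21% (50 per arm) and 24% to 26% (35 per arm), depending on the approximation used. The 10th to 90th percentile of planned n is about 36 to 563 and 31 to 738 per arm; the upper end moves by a few per cent between runs.

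**Comparison: fixed target difference, SD from this trial.** The 95% interval for the SD is about 0.88 to 1.16 times its estimate with 50 per arm (0.86 to 1.20 with 35). From end to end this changes n by (1.16/0.88)² = 1.7. By contrast, an observed d of 0.5 with 50 per arm has a 95% interval of 0.10 to 0.90, whose ends correspond to 1,570 and 20 per arm. For power to fall below 50%, the SD would have to be underestimated by the factor 1/1.43 = 0.70. In simulation this almost never occurs.

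**Allowance for uncertainty in the SD.** The one-sided 80% upper limit multiplies the estimate by √(df/χ²₀.₂₀), which is 1.067 at 98 df and 1.082 at 68 df. This raises n by 1.067² = 1.14 to 1.082² = 1.17.

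**The case against.** The strongest reply is that the sentence says less than it may seem to. The observed d is to inform the calculation together with the mean and SD; it is not said to be the sole input or to be entered as the target difference. The same section names variability as a basis for sizing and lets poor retention raise the required size. The definitive trial will need its own justification, and this article condenses a fuller protocol. This limits the point but does not answer it: the article states a use for d and names no other effect to plan on.

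A reader might infer more in three places.
- **A gate on a favourable result that biases d upward.** Section 2.1 mentions showing a trend in favor of the intervention as an aim only. The Stop-Go criterion in section 2.4 uses retention and recruitment, so no such gate exists. Requiring a positive d selects little: at a true d of 0.4, about 98% (50 per arm) and 95% (35 per arm) of pilots pass.
- **That about half of the planned trials fall below 80% power.** This is true but uninformative. Any roughly median-unbiased planning value does the same, including the SD-only approach at its point estimate (52% to 53%). Only the tail separates the two methods.
- **That the error always leads to an underpowered trial.** It also produces oversized trials.

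The plan also intends to account for baseline severity. With 50 per arm, a true d of 0.4 and an assumed correlation of 0.5 or 0.7, d/√(1−r²) is 0.46 or 0.56, and the share below 50% power falls from about 20% to about 17% or 12% to 13%. That reduces the problem without removing it. In the other direction, an assumed intraclass correlation of 0.05 in the intervention groups would widen the half-width for d slightly, from 0.40 to about 0.42 at d = 0.5.

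**Conclusion.** The point holds in a limited form. The article lists the observed Cohen's d among the inputs for the definitive sample size and names no target difference, and d is too imprecise here for that role. If d were used as the planning effect, roughly one definitive trial in five (50 per arm) to one in four (35 per arm) would have true power below 50% at a true d of 0.4. The range is 14% to 33% over true d of 0.3 to 0.5. At the other end, planned sizes of more than five times the correct one would occur in about one case in ten. These figures rest on the assumed true effects, 5% two-sided tests, 80% nominal power, no baseline adjustment and d used directly as the target. The article does not state that last rule, so they measure a risk that the wording leaves open and not a certain outcome. The article's statement that variability will support a formal calculation is sound and should stay. This trial's own conduct and analysis are not affected.

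**What to change.** In section 2.4, replace the Cohen's d sentence with one stating that:
- the target difference for the definitive trial will come from a justified minimum important difference on the chosen scale;
- this trial will supply the SD (planned at an upper confidence limit, for example one-sided 80%, about 1.07 to 1.08 times the estimate), the pre-post correlation and attrition;
- d will be reported with its 95% confidence interval as descriptive only and will not be the planning effect.

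The change is one sentence and alters nothing in recruitment, assessment or analysis. Its cost falls on the later trial, which may be planned larger than an optimistic d would suggest. A minimum important difference will also have to be justified for whichever scale is chosen.
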